## Abstract

Supplemental Digital Content is available in the text

## Introduction

1

Neck pain is a common musculoskeletal disorder that impacts individuals’ daily lives. It might sometimes lead to disabilities and an increase in medical costs. The 2010 Global Burden of Disease ranked neck pain as the fourth major factor of disability, following back pain, major depressive disorder, and other musculoskeletal disorders.^[1]^ According to a 2006 systematic review of neck pain, its prevalence in one's lifetime in adults (18–84 years) worldwide was about 50%. There are, however, regional differences,^[2]^ and women were reported to be more frequently affected by neck pain than men.^[2–4]^ The primary treatments for neck pain are oral or injected medication. While non-steroidal anti-inflammatory drugs are the most effective agents,^[5]^ they can cause adverse reactions such as gastritis, gastric ulcers, gastrointestinal bleeding, and myocardial infarctions.^[6]^

Pharmacopuncture combines acupuncture with herbal medicine, in which herbal extracts are administered on the acupoints. It can maximize and extend the effects of acupuncture by optimizing the acupoint access through an integration of physical stimulation and chemical effects.^[7,8]^ A 2016 study examined the frequency and details of different traditional treatment approaches performed in 12 Korean medicine institutions. The study found that 32,947 (98.6%) among 33,145 inpatients and 289,860 (77.6%) among 373,755 outpatients received pharmacopuncture therapy.^[9]^ A 2015 questionnaire survey of Korean medicine doctors, affiliated with Korean medicine institutions specializing in musculoskeletal disorders, reported that 95.9% of the respondents (118 out of 123) utilize pharmacopuncture for neck pain.^[10]^ According to a recent study on the status of pharmacopuncture procedures for neck pain in Korea, the most commonly performed procedure was bee venom pharmacopuncture, followed by Flos Carthami pharmacopuncture, Scolopendra pharmacopuncture, Ouhyul pharmacopuncture, Hwangryun pharmacopuncture, Corpus pharmacopuncture, Soyeom pharmacopuncture, Hwangryun-haedok-tang pharmacopuncture, and Shinbaro phamacopuncture.^[11]^

A systematic review and meta-analysis on the effects of pharmacopuncture on neck pain reported that pharmacopuncture monotherapy and pharmacopuncture-acupuncture combination therapy are significantly more effective in reducing the severity of neck pain and increasing the quality of life than acupuncture monotherapy or physical therapy (PT).^[12]^ However, existing randomized controlled trials (RCTs) on pharmacopuncture are highly heterogeneous and with a low level of evidence. It is, therefore, impossible to draw concrete conclusions on the effectiveness of pharmacopuncture therapy. A well-designed RCT that reflects the clinical context in Korea is thus needed. With this in mind, we planned a pragmatic RCT that aims to compare the effectiveness of pharmacopuncture and PT therapies on chronic neck pain.

## Methods

2

### Study design and setting

2.1

This study is a 2-armed, parallel, multi-center RCT that will be performed on 100 patients in the following institutions: Jaseng Hospital of Korean Medicine, Daejeon Jaseng Hospital of Korean Medicine, Bucheon Jaseng Hospital of Korean Medicine, and Haeundae Jaseng Hospital of Korean Medicine. Participants will be enrolled via competitive recruitment. The study protocol was approved by the institutional review board (IRB) at each institution before starting the participant recruitment process (JASENG 2019-06-009, JASENG 2019-06-010, JASENG 2019-06-011, and JASENG 2019-06-008). Further, the protocol has been registered with Clinicaltrials.gov (NCT04035018) and Clinical Research Information Service (KCT0004243) for continuous updates on the study progress. Information about the healthcare institutions and investigators can be found on the trial registration website.

### Participant timeline

2.2

On the first visit, the participants will sign an informed consent form (ICF) after receiving an explanation about the study. The examiner will screen the participants for eligibility per the inclusion/exclusion criteria. The participants will be randomized to the pharmacopuncture or the PT group during the second visit and undergo their respective treatments thereafter. The recruited participants will visit the facility 13 times, 8 of which will be treatment sessions (twice per week for 4 weeks). In-person or over-the-phone follow-up surveys will be conducted on weeks 5, 8, and 12 after treatment initiation. The schedule of enrollment, interventions, and assessments for the participants is shown in Table 1.

**Table 1 T1:**
[figure not shown]
The schedule of participants.

### Inclusion/exclusion criteria

2.3

**Inclusion criteria**

1)Neck pain for more than 6 months.2)Visual analogue scale (VAS) of neck pain more than 5.3)Age between 17 and 70 years.4)Signed informed consent.

**Exclusion criteria**

1)Patients having any of the following:2)migration of cancer reaching the spine or a fracture of the spine.3)Progressive or severe neurologic deficits.4)Cancer, fibromyalgia, rheumatoid arthritis, or gout.5)Hemorrhagic disease, stroke, myocardial infarction, kidney disease, dementia, severe diabetes or diabetic neuropathy, or epilepsy.6)Taking steroids, immunosuppressants, anticoagulants, or psychotropic medication.7)Taking non-steroidal anti-inflammatory drugs or receiving pharmacopuncture within the past week.8)Pregnant or lactating women.9)Undergone cervical surgery within the past 3 months.10)Participated in another clinical trial within the past month, or plan to participate in another trial during the follow-up period of this trial.11)Cannot write an informed consent.12)Has other difficulties in participating according to the investigator's decision.

### Interventions

2.4

#### Experimental group: pharmacopuncture

2.4.1

Pharmacopuncture therapy will be performed twice weekly for 4 weeks. One additional or fewer session per week would be allowed, depending on the patient's status. In other words, a minimum of 1 session and a maximum of 3 sessions can be performed each week. Three sessions per week might be needed in the earlier stages, during which the patient's symptoms might be severe. One session per week might suffice once symptoms have improved. The total number of sessions will not be set in advance. Rather, the physician in charge can make the clinical decisions depending on the patient's status. All procedure-related matters will be recorded in the medical chart for accurate assessment, following the methodology of a study that has analyzed the current use of pharmacopuncture therapy based on the electronic medical records in 12 Korean medicine hospitals.^[9]^ All pharmacopuncture therapies used will be retrospectively reviewed and recorded in the case report form (CRF) for analysis.

#### Control group: PT

2.4.2

A review article that used data from the Korean health insurance review and assessment service found that various types of PT (e.g., superficial heat therapy, deep heat therapy, traction, electrotherapy) are combined in clinical practice, depending on the patient's symptoms.^[13]^ Based on these data, we will allow the physician to make the clinical decisions about the type, site, and duration of PT, depending on the patient's symptoms, magnetic resonance imaging data, and degree of improvement. PT will be performed twice weekly for 4 weeks. One additional or fewer session per week would be allowed, depending on the patient's status. In other words, a minimum of 1 session and a maximum of 3 sessions can be performed each week. Three sessions per week might be needed in the earlier stages during which the patient's symptoms might be severe. One session per week might suffice once symptoms have improved. The number of sessions will be determined by the prescribing physician, depending on the patient's status. All matters pertinent to the type, duration, and site of PT will be recorded in the patient's chart for an accurate assessment. All types of treatment used will be retrospectively reviewed and recorded in the CRF for analysis.

### Criteria for discontinuation and withdrawal

2.5

The trial can be discontinued for a participant under the following conditions:

1)discovery of an illness that had not been detected at the baseline assessment and might impact the evaluation of the study results.2)Request to discontinue the study by the participant or by the participant's legal representative, or withdrawal of the consent by the participant during the study period.3)Confirmation of pregnancy during the study.4)Presence of problems related to undergoing medical or Korean medical procedures for neck pain.5)Other conditions in which the continuation of participation in the study is deemed inappropriate by the investigator in charge.

### Concomitant treatment

2.6

Patients can seek drug therapy and care at another healthcare institution in cases of severe pain during the treatment or the follow-up period. The details and frequency of such treatments will be recorded thoroughly in the CRF and used for the analysis.

### Outcomes

2.7

#### Primary outcome: VAS of neck pain

2.7.1

The VAS is one of the means for estimating the patient's pain. It is an instrument consisting of a straight 100-mm line with the left-most point indicating no pain and the right-most point indicating the most excruciating pain one can imagine. Each patient would mark the position that best represents the level of her or his pain. At each assessment, the patients would mark a point on the line that represents their neck pain during the preceding week.

#### Secondary outcome

2.7.2

##### Northwick Park questionnaire (NPQ)^[14]^

2.7.2.1

The NPQ is a self-reported questionnaire, consisting of 9 items about daily life activities that are influenced by neck pain (intensity, sleep, numbness, duration, carrying things, reading/watching TV, working, social activities, and driving). Each item consists of 1 question and 5 responses that indicate growing levels of difficulty and pain rated from 0 to 4, with 4 indicating the most significant functional impairment. The total score is a sum of the scores for all 9 items. In the present study, we will use the Korean version of the NPQ, which was translated and validated by Lee et al in 2010.^[15]^

##### VAS of pain radiating to the arm

2.7.2.2

The VAS, as described above, will be used to assess the patients’ pain radiating to the arm. The patients would mark a point on the line that represents their radiating arm pain during the preceding week.

##### Numeric rating scale (NRS) of neck and arm bothersomeness

2.7.2.3

The intensity of discomfort in the neck and upper arm area during the past week will be assessed using the NRS. Patients will choose a number between 0 to 10 that best represents their level of discomfort, with 0 being no pain and 10 being the most excruciating pain one can imagine.

##### Neck disability index (NDI)^[16]^

2.7.2.4

The NDI was developed to examine the level of disability caused by neck pain in daily life. Ten items are scored, with each item being rated from 0 to 5. The NDI is calculated by dividing the total score by the number of scored items.

##### Patient global impression of change^[17]^

2.7.2.5

The Patient global impression of change is a subjective evaluation of the level of improvement by the patients:

1.very much improved2.much improved3.minimally improved4.no change5.5 minimally worse6.much worse7.very much worse

##### Short form-12 health survey (SF-12) version 2

2.7.2.6

The SF-12 is a questionnaire for assessing health-related quality of life. It consists of 12 items in 8 domains: physical functioning, role-physical, bodily pain, general health, vitality, social functioning, role-emotional, and mental health. It takes less than 5 minutes to complete the survey, and a higher score indicates a better health-related quality of life. In the present study, we will use a validated Korean version of the SF-12.^[18]^

##### 5-level EuroQol-5 dimensions (EQ-5D-5L)

2.7.2.7

The EQ-5D-5L is an indirect measure of the quality weights of particular health conditions by appraising health status from multidimensional aspects and using the pre-designated preference weights for each functional level. It is the most widely used indirect measure instrument. The EQ-5D-5L is comprised of 5 dimensions (mobility, self-care, usual activities, pain, anxiety/depression), and the level of each dimension is surveyed. Weighted values are designated according to each dimension's level, and the preference score is calculated based on these weights and specific constants.^[19]^

##### Costs data

2.7.2.8

To measure costs, we will use a survey, comprising of items that will estimate direct medical costs (healthcare service), direct non-medical costs (purchasing foods, medical devices, and transportation fee), and indirect costs (time cost and loss of productivity). Loss of productivity are defined as the financial loss caused by the inability to work due to the disease itself or premature death from the disease. Loss of productivity will be measured using the work productivity and activity impairment questionnaire,^[20]^ and the value will be converted to a cost to be used in the cost-effectiveness analysis.

##### Drug consumption

2.7.2.9

The types and doses of drugs (rescue drugs) that the participants took for neck pain during the study period will be identified via a survey during their respective visits. Other types of therapies, such as other PT and injections, will be recorded as if they were sessions received.

### Adverse events

2.8

For safety assessment, white blood cell, neutrophil, lymphocyte, monocyte, eosinophil, basophil, red blood cell, hemoglobin, hematocrit, mean corpuscular volume, mean corpuscular hemoglobin, mean corpuscular hemoglobin concentration, platelet, erythrocyte sedimentation rate, total protein, albumin, total bilirubin, alkaline phosphatase, aspartate aminotransferase, alanine aminotransferase, gamma-glutamyl transpeptidase, and C-reactive protein will be performed before the start and after the end of treatment sessions in both study groups to compare the incidence of adverse events between groups.

An adverse event refers to undesirable and unintended signs, symptoms, or diseases that would occur after a procedure. It includes responses that are not directly related to the procedure. In the present study, we will collect data on adverse events based on the patients’ reports of symptoms and our observations. We will then analyze the incidence of adverse events that are suspected to be related to the treatment. This would include abnormal laboratory results and serious adverse events. The causality between the treatment and the adverse events will be assessed based on a 6-point scale, following the world health organization-Uppsala monitoring center causality assessment system (1 = definitely related, 2 = probably related, 3 = possibly related, 4 = probably not related, 5 = definitely not related, and 6 = unknown). The severity of all adverse events will be classified into 3 levels following the Spilker classifications:

(1)Mild, does not need treatment or does not significantly impair daily activities (functions)(2)Moderate, significantly impairs daily activities (functions) and may require treatment but resolves afterward(3)Severe, a serious adverse event that requires intensive treatment and leaves sequelae.

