### Data monitoring

2.15

The data monitoring will be performed to examine the safety of participants and the clinical data's completeness. This monitoring will be done by comparing the CRF and the source documents and by reviewing participants’ safety data. Routine monitoring visit will be conducted 4 times, and closing-out visit will be done once at each site during the trial. Trial steering group will meet to review conduct throughout the trial period once every 2 months. The data monitoring committee was not organized as no severe AE regarding pharmacopuncture or PT previously reported are expected to occur. The interim analysis will not be done in this study.

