### Stopping rules

2.16

The trial might be discontinued at any point upon discovery of an unexpected, evident or unacceptable risk for participants, or upon the occurrence of serious adverse events, presumed to be related to pharmacopuncture or PT, in more than 25% of the participants.^[23]^ The PI would make the final decision if to discontinue the study.

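### The three adverse event severity grades in section 2.8 mix intensity, seriousness and outcome, and are neither exclusive nor exhaustive

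*Protocol article*

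**What the plan says.** Section 2.8 of the protocol article sets one scale for every event: "The severity of all adverse events will be classified into 3 levels following the Spilker classifications". The grades are printed as:

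- "Mild, does not need treatment or does not significantly impair daily activities (functions"
- "Moderate, significantly impairs daily activities (functions) and may require treatment but resolves afterward"
- "Severe, a serious adverse event that requires intensive treatment and leaves sequelae"

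Earlier in the same section, when describing the analysis of events suspected to be related to treatment, the article adds: "This would include abnormal laboratory results and serious adverse events". It gives no criteria there for what makes an event serious.

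Section 2.16 allows the trial to be stopped "upon the occurrence of serious adverse events, presumed to be related to pharmacopuncture or PT, in more than 25% of the participants". It also allows stopping at any time if an unacceptable risk comes to light, with no count attached.

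Section 2.17 plans to compare the groups on the percentage of patients with any adverse event, by Chi-squared or Fisher test.

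**The concern.** A severity grade should say how intense an event was. Whether the event was serious, and how it ended, are separate facts. The printed grades put all three on one scale. Severe contains the word *serious* and also requires a lasting effect. Moderate requires resolution. Mild is met by either of two conditions joined by 'or'.

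Two things are at stake. First, sites that follow the wording exactly could grade the same event differently, or find no grade for it. A table of events by severity could then make harm look milder than it was. Second, the Severe grade is the only place where the article describes a serious event. A site could take it as the working definition when it decides what counts toward section 2.16.

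**Working it through.** The documents give no figure to reproduce here, so the check is logical. Read as written, the grades require:

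- Mild: no treatment needed, **or** no significant impairment.
- Moderate: significant impairment **and** resolution. Treatment is optional.
- Severe: serious **and** intensive treatment needed **and** sequelae.

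Take events that significantly impair function, and treat an event that does not resolve as one that leaves sequelae. Three levels of treatment by two outcomes give 3 × 2 = 6 combinations.

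| Treatment needed | Outcome | Grade(s) whose wording is met |
|---|---|---|
| none | resolves | Mild and Moderate |
| none | does not resolve | Mild |
| ordinary | resolves | Moderate |
| ordinary | does not resolve | no grade |
| intensive | resolves | Moderate |
| intensive | does not resolve | Severe, if also judged serious |

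So 1 of 6 meets two grades and 1 of 6 meets none. Another 2 of 6 receive a grade that understates them: the lasting impairment called Mild, and the intensively treated event called Moderate. The remaining 2 are graded as one would expect.

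Events that do not impair function all satisfy Mild through the 'or'. That includes a laboratory abnormality of any size, even one that needs treatment, and section 2.8 includes abnormal laboratory results among the events it analyses.

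Moderate and Severe both depend on how the event ends, so neither can be finally assigned at onset. The article does not say when grades are fixed.

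**Effect on the stopping count, conditional only.** Suppose sites counted only events that meet the Severe wording. With 100 planned participants, 25% is 25, so more than 25% needs at least 26. Let *p* be the true rate of related serious events and *s* the share of them that meet the Severe wording. The documents give neither, so both are assumed. The chance of reaching the threshold is P(X ≥ 26) with X ~ Binomial(100, *p* × *s*):

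| *p* | *s* = 1 | *s* = 0.75 | *s* = 0.50 |
|---|---|---|---|
| 5% | about 0 | about 0 | about 0 |
| 30% | 0.84 | 0.23 | 0.003 |
| 40% | 0.999 | 0.84 | 0.09 |

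If serious events are identified independently of the grade, the *s* = 1 column applies and the wording of the grades has no effect on the rule.

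**The case against.** A reader might infer that the stopping rule undercounts, or that every event needing hospital-level care that resolves drops out of the serious-event count. The documents do not support either. The Severe wording makes severe events a subset of serious ones and does not define serious as severe. An event graded Moderate can still be a serious adverse event. Section 2.8 names serious adverse events apart from the scale, and section 2.16 counts them without mentioning the Severe grade. Its other trigger would cover a dangerous reaction that resolved.

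A reader might also tie the grades to the absence of a monitoring committee, for which section 2.15 says: "The data monitoring committee was not organized as no severe AE regarding pharmacopuncture or PT previously reported are expected to occur". That sentence is about what has been reported before, and nothing shows that those events were graded on this trial's scale. The link does not hold.

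The article also condenses a fuller protocol (version 1.5, section 3.1), and mentions standard operating procedures (section 2.13) and training in good clinical practice (section 2.19). Criteria for seriousness and an outcome field may well be found there, so their absence from the article is not the complaint. The planned group comparison in section 2.17 does not use severity.

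All of this stands, and it limits the consequences. It does not repair the scale. The three definitions are printed in the article, and a seriousness definition elsewhere would not make them exclusive or complete.

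**Conclusion.** The point holds as a faulty stated rule for grading severity. Among events that impair function, 4 of the 6 combinations of treatment and outcome are double-graded, ungraded or graded too low. This follows from the wording and needs no assumed event rate. It does not say how many actual events will be affected, which the documents cannot show.

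The direct consequence is for the severity distribution, which could understate harm. The planned comparison of any adverse event between groups is untouched. A consequence for section 2.16 is conditional: the count could be too low only if sites identify serious events through the Severe grade, which the text leaves open but does not require.

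**What to change.** In section 2.8, grade severity by intensity only:

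- Mild: replace 'or' with 'and'.
- Moderate: remove the closing clause about resolution.
- Severe: remove the reference to a serious event and the requirement of sequelae.

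Those edits alone would leave an event that needs ordinary treatment without impairing function in no grade, and an impairing event needing intensive treatment in both Moderate and Severe. To make the categories exclusive and complete, Moderate should also be worded as impairment or need for treatment, short of intensive treatment. The combinations of impairment (2) and treatment (3) then give 1 Mild, 3 Moderate and 2 Severe, with no gap or overlap.

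Record seriousness and outcome as items separate from severity. Reconcile section 2.8 with section 2.16 by stating that the stopping rule counts the seriousness item and not the Severe grade.

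The cost is minor wording in the protocol and case report form, with no extra visits or participants. Events already graded need re-review, because intensity, seriousness and outcome cannot be recovered from a single grade.
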